## Abstract

**Background:**

The NHS Bowel Scope Screening (BSS) programme offers men and women aged 55 years a once-only flexible sigmoidoscopy (FS), a test that can help reduce colorectal cancer (CRC) incidence and mortality. However, the benefits of BSS are contingent on uptake. This National Institute for Health Research-funded single-stage phase II trial will test the feasibility of using patient navigation (PN), an intervention that offers support to patients to overcome barriers to healthcare, to increase BSS uptake within a socially deprived area of England.

**Methods/design:**

All individuals invited for BSS at South Tyneside NHS Foundation Trust during the 6-month recruitment period will be invited to take part in the study. Consenting participants will be randomised to receive PN or usual care in a 2:1 ratio. PN involves non-attenders receiving a phone call from a Specialist Screening Practitioner (SSP) who will elicit reasons for non-attendance and offer educational, practical, and emotional support as needed. If requested by the patient, another appointment for BSS will then be arranged. We anticipate 30 % of participants will be non-attenders. Using A’Hern single-stage design, with 20 % significance level and 80 % power, at least 35 participants who receive PN need to subsequently attend for PN to be considered worthy of further investigation in a definitive trial. The primary outcome measure will be the number of participants in the PN group who re-book and attend their BSS appointment. A qualitative analysis of the PN transcripts, and interviews with the SSPs, will also be conducted, alongside a quantitative analysis of completed patient-reported experience questionnaires. An economic analysis will calculate the costs of delivering PN.

**Discussion:**

This feasibility study will be instrumental in deciding whether to conduct the first definitive trial of PN in BSS in England. If PN is subsequently shown to be cost-effective at increasing uptake of BSS, NHS policies could be modified to implement PN as a standard service. The results will be disseminated in peer-reviewed journals and at scientific conferences.

**Trial registration:**

International Standard Randomised Controlled Trial Number, ISRCTN13314752

**Electronic supplementary material:**

The online version of this article (doi:10.1186/s40814-016-0093-8) contains supplementary material, which is available to authorized users.

## Background

Colorectal cancer (CRC) is the fourth most common cancer and the second leading cause of cancer death in England [1]. CRC screening can help detect cancer early, when it is more easily treated, subsequently helping to reduce CRC mortality rates [2, 3]. In England, the National Health Service (NHS) runs an organised population-based CRC screening programme (Bowel Cancer Screening Programme, BCSP) which offers biennial screening via guaiac-based faecal occult blood testing (gFOBt) to men and women aged 60–74. In March 2013, the BCSP additionally started the national roll-out of the ‘Bowel Scope Screening (BSS) Programme’, which offers men and women a single flexible sigmoidoscopy (FS) examination at age 55. The UK FS trial has shown that a single FS examination, with its capacity to remove any pre-malignant growths, reduces CRC mortality by 43 % and incidence by 33 % [4].

Similar to all cancer screening programmes, the benefits of BSS are largely dependent on high uptake; in the current BCSP using gFOBt, only 54 % of people invited to do the gFOBt return a completed kit [5]. Findings from a meta-analysis and a pathfinder study suggest that uptake of BSS is likely to be as low as gFOBt, undermining the potential of the programme [6, 7]. Analyses of uptake data from the first 14 months of the BSS programme roll-out in six pilot centres indicated uptake to be only 43.1 % [8]. BSS participation has also been found to be strongly socially graded, ranging from 32.7 % in the most deprived to 53.2 % in the least deprived area quintiles, resulting in an urgent need to develop effective interventions to promote BSS uptake, particularly among lower SES groups.

Patient navigation (PN) involves specially trained individuals giving tailored support to patients to overcome barriers personally preventing them from optimising their healthcare along the cancer pathway. PN can take on many communication formats, e.g. face-to-face or over the telephone, and includes the delivery of clear information and practical guidance and advice to the individual, in an emotionally supportive context [9]. PN has been shown to increase cancer screening participation in the USA, including CRC screening [10–13]. It is particularly effective among ‘hard-to-reach’ groups but has also been effective in the general population. A recent trial found benefits associated with PN over-and-above providing an organised screening programme [13]. In the UK, PN has currently only been employed in a breast cancer screening context, with results showing an increase in uptake among African Caribbean women, in two socially diverse areas of London [14].

Incorporating PN within a CRC screening context in the UK, and providing a more personal and interactive approach to communicating information about BSS, may circumvent many barriers to CRC screening. Evidence from the gFOBt screening programme suggests that older adults, particularly those with low literacy, have difficulty in extracting what they need from the current information materials [15–17]. There is also a lack of public awareness of CRC as a common cancer and of the primary aim of BSS in preventing rather than diagnosing CRC [18].

Logistical barriers to preparing for, and participating in, hospital-based BSS appointments have also been identified. For example, difficulties have been found in comprehending instructions for home-administered enemas for bowel preparation, particularly for those with low literacy, even though it is reasonably acceptable among the public [19, 20]. There are also some well-recognised emotional barriers including fear of the test and cancer diagnosis and fatalistic attitudes [21]. Helping to manage feelings and fears associated with cancer is one of the main tasks addressed by patient navigators alongside access to care and other logistical issues (e.g. transportation) [9, 22].

## Methods/design

### Design

A single-stage phase II trial will test whether PN is likely to meet the basic level of efficacy (in this case by increasing uptake), is practical and acceptable within a UK setting and is therefore worthy of further investigation in a large-scale RCT [24]. To enhance the opportunity to conduct PN with individuals who do not confirm or attend their appointment, while keeping SSP workload to a minimum, a randomisation ratio of 2:1 will be used in favour of the intervention group (vs. usual care). The aim of the trial is not to make a direct comparison between the intervention and control groups but rather to consider the level of uptake in the PN group, while also assessing patients’ acceptability and willingness to be randomised. The CONSORT diagram is shown in Fig. 1.

**Fig. 1 Fig1:**
[figure not shown]
CONSORT flow diagram outlining the study procedure (with estimated numbers)

The design of this protocol has followed the recommendations of the Standard Protocol Items: Recommendations for Interventional Trials (SPIRIT) guidelines [25, 26]. A full copy of the SPIRIT guidelines checklist can be found in Additional file 1.

### Recruitment and setting

Recruitment will be conducted through the South of Tyne Screening Centre. The Screening Centre operates across three sites with one site, South Tyneside District Hospital (STDH), involved in this current study. Approximately, 40 people each week are invited to have BSS at STDH. All individuals invited for BSS at STDH will also be invited to take part in this study (see Fig. 2). There are no study exclusion criteria; however, only individuals who return a study consent form with their contact details, including telephone number(s), will be able to participate in this study. Recruitment will occur over a 6-month period.

**Fig. 2 Fig2:**
[figure not shown]
Positioning of the intervention within the structure of the BSS programme

### The intervention

The PN intervention will consist of at least one telephone call that will begin with the SSP introducing themselves and the purpose of the call. The SSP will use open-ended and non-threatening questions to elicit reasons for the patient’s non-attendance/non-confirmation and their motivation to attend BSS in the future. If the patient appears interested in BSS, the SSP will reiterate its benefits and offer solutions to any identified barriers (e.g. an earlier appointment time or assistance with the enema). In the role of navigator, the SSP should provide two types of support: practical/instrumental and emotional/relationship [27]. The SSPs will receive training on what PN is and how it should be delivered during this study. A manual will be developed to supplement the training and provide a resource for SSPs. The training will be assisted by a patient representative who will conduct role play scenarios and provide feedback to the SSPs. The navigator should refer to the manual for instrumental support options but use their communication and interpersonal skills to offer emotional support and strengthen the relationship between the hospital and the patient.

### Procedure

The Screening Centre hub, where all BSS invitations are packed and prepared for mail out, will oversee the study invitation process. During the recruitment period, the hub staff will insert a study invitation envelope to the standard BSS pre-invitation letter sent to all eligible individuals. The BSS pre-invitation letter briefly introduces BSS and forewarns of an additional letter being sent in a further 2 weeks, which will formally invite the individual to attend a BSS appointment at a specific date and time (see Fig. 2 for the BSS invitation process). The study invitation envelope will contain a participant information sheet (PIS), a consent form, a pre-paid return envelope, and a non-participation postcard. The PIS will provide information about the aim of the research study and detailed information about the consent process, data protection and study procedure, including the telephone number that will show on their caller display if they were to receive a call from an SSP. It will be made clear that the decision to participate in the study is separate to the decision to take part in screening. Each consent form will have a unique study ID attached to it, and hub staff will note which study ID corresponds to each person invited. To take part in the study, participants will be asked to complete and return the consent form to the Research Nurse (RN) at STDH in the return envelope provided. Those not wanting to take part in the study will be invited to indicate their reason on the non-participation postcard and return it freepost to the researchers.

By offering consent, participants will be agreeing to share their contact details with the assigned RN and to be potentially contacted by a SSP. The RN will contact the hub staff to confirm the NHS number of those consenting to take part in the study, using the unique study ID. Once the RN has the NHS numbers, they can then use the web-based national Bowel Cancer Screening System (BCSS) within STDH to follow each participant along the BSS pathway and obtain their BSS confirmation and attendance status.

On receipt of each consent form, the RN will consult a pre-generated randomisation list to determine which study group each participant should be allocated to. Two randomisation lists (one for each gender) will be generated by a medical statistician, who will randomly allocate participants to receive either PN or usual care with a ratio of 2:1 favouring the intervention. It is not possible to blind the RN and SSPs to each participant’s study group allocation. However, the participants themselves will only know the group they have been allocated to when they receive either a navigation phone call or their end-of-study questionnaire (ESQ): the ESQ will be accompanied by a cover letter thanking them for their participation and informing them of their group allocation.

The RN will work with University College London (UCL) researchers and SSPs and use the BCSS to document all activities of consenting participants on a database devised for this study (e.g. group assignment, original appointment date and subsequent changes made, attendance status, date of ESQ mail out, and date of receipt of completed ESQ). This will allow the RN to monitor who is eligible for PN and to obtain important information for establishing the feasibility of the study design and expectations for the larger RCT.

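### The Research Nurse who receives the consent forms also reads the randomisation lists, and no described step hides the next allocation until a participant is entered

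*Protocol article*

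**What the plan says.** The relevant statements are in the protocol article, under Procedure unless noted.

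- **Receipt of forms:** "participants will be asked to complete and return the consent form to the Research Nurse (RN) at STDH in the return envelope provided".
- **Allocation:** on receiving each form, "the RN will consult a pre-generated randomisation list to determine which study group each participant should be allocated to".
- **Source of the sequence:** "Two randomisation lists (one for each gender) will be generated by a medical statistician", "with a ratio of 2:1 favouring the intervention". Trial status reports a later change to 4:1.
- **Blinding:** "It is not possible to blind the RN and SSPs to each participant’s study group allocation".
- **Further handling:** "The RN will contact the hub staff to confirm the NHS number of those consenting to take part in the study". With that number the RN can follow confirmation and attendance on the national screening system.
- **Entry condition (Recruitment and setting):** there are no exclusion criteria, but "only individuals who return a study consent form with their contact details, including telephone number(s), will be able to participate in this study".

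The article mentions no central or remote allocation service, no sealed envelopes, and no log to be completed before the list is read.

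**The concern.** Having a statistician generate the sequence protects it from being made up on site. It does not conceal it. Concealment requires that whoever enters participants cannot know the next assignment until entry is fixed. Here the same person receives the form, can see whom it is from, and looks up the arm.

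Postal self-consent removes the usual route to selection bias, because nobody chooses whom to approach. Two smaller routes remain:

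- **Order.** If two or more forms for the same gender list are in hand, the order in which they are taken decides who gets which arm.
- **Completeness.** A form without a usable telephone number cannot lead to participation. Someone has to decide whether it is set aside, queried or accepted, and the RN is the only recipient named.

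What depends on comparable arms is the between-group analysis of the end-of-study questionnaire (Quantitative analysis), which uses inferential statistics, and the uptake described by arm to inform phase III sample size (Primary analysis). The study is also meant to establish whether the design is feasible for the larger trial, so this allocation procedure is itself being piloted.

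**Working it through.** This is mainly a matter of setting statements side by side. Arithmetic only helps with scale.

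**1. Who knows what, and when.** The form goes to the RN. The RN consults the list when the form arrives. The list already exists at that point. Nothing described separates the decision that a form is valid from the sight of the allocation. As printed, the next assignment on each gender list can therefore be known before the next form is entered.

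**2. How often forms could arrive together.** Sample size gives 960 invited and 40% consenting: 960 × 0.40 = 384, as stated. Recruitment lasts 6 months.
- Over 26 weeks: 384 / 26 = 14.8 consents a week.
- At the article's 40 invitations a week, 960 / 40 = 24 weeks, and 384 / 24 = 16 a week.
- Split evenly between two gender lists (an assumption): about 7 to 8 a week per list.

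Forms for the same list arriving together are plausible at the planned rate. Trial status reports lower consent than expected, so in practice this will happen less often.

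**3. What seeing the list adds.** A person who can read it knows the next assignment with probability 1. Without it, and with simple randomisation, the best guess is always navigation. That guess is right with probability 2/3 at 2:1 and 4/5 at 4:1, and because it never changes it gives nothing to steer by.

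The article does not say whether blocks were used. If they were, an RN who knows past assignments could guess better. For a block of 3 at 2:1:
- first place: 2/3
- second place: (2/3 × 1/2) + (1/3 × 1) = 2/3
- third place: 1
- average: (2/3 + 2/3 + 1) / 3 = 0.78

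The same calculation gives 0.74 for a block of 6 at 2:1 and 0.84 for a block of 5 at 4:1. These block sizes are assumptions.

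**4. What does not change.** The stated 77 non-attenders allocated to navigation (384 × 0.30 = 115.2, given as 116; 116 × 2/3 = 77.3) and the cut-off of 35 do not depend on how allocation is concealed.

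**The case against.** **The article may be condensing.** How a list is held and revealed is often left to a full protocol, and consulting a list is compatible with several ways of holding it. The article does not call the list open. It does not say that the RN judges completeness or chooses the order of entry, and allocation on receipt of each form suggests working form by form. This stands in part: those readings are inferences. But the article does state who consults the list and when, and that mechanism as printed is not a concealed one.

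**The blinding sentence is about something else.** "It is not possible to blind the RN and SSPs" concerns assignments already made. That is correct, and it does not show that future assignments are visible. Equally, it gives no reason why they should be.

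**There is little to steer on.** Forms go out with the pre-invitation letter, before any appointment is offered. To affect the primary count, the RN would have to foresee both who will miss an appointment and who could then be persuaded. This stands and is the main reason for calling the risk modest.

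**Stronger readings a reader might infer.**
- *That steering could materially raise the chance of reaching 35 attenders.* The article gives no null or target re-attendance rate and no basis for any shift. If steering only re-sorts a fixed pool of non-attenders, lifting the navigation arm by d points lowers usual care by 2d at 2:1, since 2/3 × d = 1/3 × 2d, and by 4d at 4:1. A 3-point lift would then need a gap between arms of 9 or 15 points. Ordering forms that arrive together is not a plausible source of such gaps.
- *That steering would leave no trace.* The hub records which study ID belongs to each person invited, and the study database records group assignment. That is an imperfect audit trail, but it is one.
- *That steering has occurred.* Nothing in the article suggests it.

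**Conclusion.** The point holds as a weakness in the stated procedure. One unblinded person receives identifiable consent forms and reads the allocation list, and nothing described hides the next assignment until entry is fixed.

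The consequence is limited. The Design section says that comparing the arms directly is not the aim, and the primary outcome counts people within the navigation arm. The exposure is mainly in the questionnaire comparisons, in the by-arm uptake that feeds phase III planning, and in carrying an unconcealed procedure into a definitive trial, where the comparison between arms would be the main result.

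No size can be put on any bias from the document. The conclusion rests on two reasonable inferences: that the RN can see upcoming entries when consulting the list, and that the RN, as the only named recipient, handles incomplete forms. If a fuller document shows a concealment step, the point reduces to reporting it.

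**What to change.** Have the trial statistician or the UCL researchers hold both gender lists, including those now in use at 4:1. For each returned form the RN first records study ID, gender, date of receipt and whether the form is complete. Only then is that participant's allocation sent. If blocks are used, the block size should not be disclosed to the RN. State the procedure in the protocol and carry it into the definitive trial. Recruitment already completed cannot be changed, but data collection is described as ongoing, so any consents still to come can be protected.

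The cost is a log entry, one extra message per consent, someone to answer it, and a short delay before allocation. The delay does not affect navigation, which begins only after non-confirmation or a missed appointment. On the letter schedule in Usual care group, the earliest of these comes about 2 + 2 + 2 = 6 weeks after the study pack is sent.

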#### Intervention group

Individuals in the intervention group will also follow the above usual care process. However, if an individual either fails to confirm or attend a confirmed appointment (‘non-attenders’), they will, in addition to the cancellation/DNA letter, enter a navigation episode, whereby a SSP trained in PN will make up to three attempts to contact the individual by telephone. All call attempts will be documented and, if contact is made, the SSP will establish the reasons for non-attendance, offer support and, if suitable, arrange a new appointment. The navigation episode could involve multiple telephone conversations and closes when a decision to arrange a new BSS appointment, or not, is made. Participants in the PN group will only be eligible for one navigation episode, i.e. if a further BSS appointment is made following PN, but is not attended, only a further ‘DNA’ letter is sent, as per standard practice: no additional navigation call attempts will be made.

All consenting participants will be sent an ESQ, with a freepost-return envelope, either 4 weeks following an attended appointment or 1 week after a non-attended appointment or final PN call (see Fig. 3). There will be four versions of the ESQ with questions varying depending on the participant’s study group and BSS attendance status. The aim of the ESQ is to assess participants’ knowledge of BSS and their satisfaction with their choice to attend screening or not. The ESQ for those receiving PN also aims to find out how participants felt about this process (e.g. their perceptions of the usefulness of PN and how it made them feel) and the effect PN has on various psychosocial variables such as informed choice and BSS knowledge [28–36]. If ESQs are not returned within 2 weeks, a reminder ESQ with a freepost-return envelope will be sent.

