### Sample size

Currently, there is no directly comparable evidence to estimate the number of people who will consent to take part in this study. Because our sample is likely to consist of people who support the BSS in principle, we have used recruitment figures from the UK FS trial as a guide to estimating our recruitment rate.

South of Tyne Screening Centre will invite approximately 960 people for BSS at STDH during the recruitment period. In the UK FS trial, 55 % of those initially approached were interested in receiving a FS examination [37]. Given that people in this study will receive an invitation for BSS regardless of their response to our invitation, recruitment may be lower (i.e. 40 %; *N* = 384).

It is likely that uptake among this self-selected sample would be higher than for the general population. On the basis of the UK FS trial, we predict that about 70 % of the sample would attend their original appointment as part of the usual pathway. The remaining 30 % of consenting participants would fail to attend their appointment (*N* = 116) of whom we would allocate two thirds (*N* = 77) to receive PN.

Using A’Hern single-stage design, with 20 % significance level and 80 % power, at least 35 participants would need to re-schedule and subsequently attend their appointment for PN to be considered worthy of further investigation [24].

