### Outcome measures

The primary outcome measure of this study will be the number of non-attenders in the PN group who are navigated and then re-book and attend their new BSS appointment.

Additional outcomes measures will include the following:Barriers to BSS attendance: All PN sessions will be audio recorded (with patient permission) and transcribed. An analysis of the transcripts will aim to highlight all the barriers to attendance described by patients and the extent to which they are modifiable.An evaluation of the PN process: Approximately seven SSPs will be assigned to this study. SSPs will monitor the number of contact attempts made and the duration of telephone calls made within each navigation episode. The audio recordings of the navigation calls will also be analysed with regard to the SSPs adherence to the PN manual, the type of support given (e.g. practical and/or emotional), and the action plans agreed with patients. Exit interviews with SSPs will be conducted, audio recorded and analysed with the aim of ascertaining their views on the PN process. Exit interviews will either be conducted face-to-face within the hospital setting or over the telephone, whichever is most convenient for each SSP.Patient-reported outcomes: Completed ESQs will be analysed to ascertain the number of people making an informed choice in both groups and, where relevant, satisfaction with the BSS procedure and PN intervention.Reasons for not participating in the study: A brief freepost-return A5 postcard will be provided within the study invitation envelope that will be sent alongside the BSS pre-invitation letter. The postcard will give those not wanting to take part in the study the option to choose among reasons for non-response/refusal (e.g. ‘I do not want to share my personal details with the researchers’, ‘I did not think I will need any support’), with responses considered in the development of the RCT.Economic analysis: We will calculate the cost of delivering the PN intervention, including SSP time, and training. We will also plan the economic evaluation that would accompany the full RCT.

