#### Quantitative analysis

Data collected on the study database and from returned non-participation postcards will be analysed and mainly reported as descriptive data (e.g. attendance rates, time for return of ESQs, number of people selecting specific reasons for non-study participation). The ESQ data will be analysed using a mixture of descriptive and inferential statistics including chi-square analysis and linear and logistic regression so that predictors of attendance and non-attendance can be investigated, as can between group differences in views, attitudes, knowledge and satisfaction with BSS. Results will be presented with a 95 % confidence interval.

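### The letter enclosed with the end-of-study questionnaire tells participants their group before they answer, which puts the planned between-group questionnaire comparisons at risk of response bias

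*Protocol article*

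**What the plan says.** Under Procedure, the protocol article states that "the participants themselves will only know the group they have been allocated to when they receive either a navigation phone call or their end-of-study questionnaire". The questionnaire is "accompanied by a cover letter thanking them for their participation and informing them of their group allocation".

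Under Intervention group it adds "All consenting participants will be sent an ESQ, with a freepost-return envelope", with a second copy going out if nothing comes back within 2 weeks. The form is not the same for everyone: "There will be four versions of the ESQ with questions varying depending on the participant’s study group and BSS attendance status".

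The answers are then compared by arm. Outcome measures says "Completed ESQs will be analysed to ascertain the number of people making an informed choice in both groups". Quantitative analysis lists chi-square tests and linear and logistic regression, among other things to examine "between group differences in views, attitudes, knowledge and satisfaction with BSS", with 95% confidence intervals. The article gives no reason for disclosing the group together with the questionnaire rather than after its return.

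**The concern.** Anyone who has not had a navigation call has not been told their group when the ESQ arrives. That covers the whole usual-care arm and everyone in the navigation arm who attended as first booked. The letter tells them in the same envelope as the self-report instrument. Satisfaction, views and attitudes are then reported, and the form returned or not, with the group known.

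The clearest exposure is among original-appointment attenders. Both arms follow the usual pathway until non-attendance, so these people have the same planned care in either arm. Apart from chance, a difference between arms in their answers or return rates would be expected to reflect the disclosure itself, or differences between the questionnaire versions. Without the letter, this contrast would be close to clean.

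The analysis cannot remove the problem afterwards, because being told one's group and being in that group coincide for everyone who receives the letter. Return rates matter too: the study database records ESQ receipt, and it is meant to inform expectations for the larger trial.

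**Working it through.** **Inputs** (protocol article, Sample size unless stated)
- Invited: "South of Tyne Screening Centre will invite approximately 960 people for BSS at STDH during the recruitment period".
- Consent 40%, attendance at the original appointment 70%, non-attendance 30%.
- Two thirds of non-attenders in the navigation arm (2:1). The ratio is now 4:1 (Trial status).
- Up to three telephone attempts per non-attender, with no contact rate given (Intervention group).
- No ESQ return rate is given.

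**The plan's own flow reproduces**
- Consenting: 960 × 0.40 = 384.
- Non-attenders: 384 × 0.30 = 115.2, stated as 116.
- Non-attenders in the navigation arm: 116 × 2/3 = 77.3, stated as 77.

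**Share with no navigation call when the ESQ arrives, if every navigation-arm non-attender is reached**
- At 2:1: (384 − 77)/384 = 307/384 = 79.9%.
- At 4:1 throughout: 1 − 0.30 × 0.80 = 76%.
- Half recruited at each ratio (assumption): 1 − 0.30 × (0.667 + 0.80)/2 = 78%.

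**Who the 307 are, at 2:1**
- Original-appointment attenders, both arms: 384 − 116 = 268 (70% of 384).
- Usual-care non-attenders: 116 − 77 = 39 (10% of 384).
- By arm: navigation 256, of whom 256 − 77 = 179 (70%); usual care 128, all of them.

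**Sensitivity to the contact rate c (assumed range 50% to 90%)**
- At 2:1: 1 − 0.20c gives 90% down to 82%.
- At 4:1: 1 − 0.24c gives 88% down to 78%.

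**Sensitivity to the return rate**

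Let k be the return rate of navigated participants divided by that of the others, and a the navigated share (0.20 at 2:1, 0.24 at 4:1). Among those who return the ESQ, the share not navigated is (1 − a)/[(1 − a) + a·k].

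| k (assumed) | 2:1 | 4:1 |
|---|---|---|
| 0.5 | 89% | 86% |
| 1 | 80% | 76% |
| 2 | 67% | 61% |

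The 80% figure is therefore a share of consenting participants. It is a share of respondents only if return rates are equal.

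**The case against.** The strongest case on the other side has five parts.

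- **Low stakes.** The Design section says that comparing the arms directly is not the aim, and Primary analysis says the study is not powered for it. Attendance comes from the screening system. This stands as a limit on importance: neither the primary outcome nor the threshold of 35 is touched. It does not withdraw the between-group ESQ analyses, which Quantitative analysis still plans.
- **The letter is not the only source of knowledge.** Navigated participants know their group in any case. The information sheet mentions a possible call, so a usual-care non-attender who got none may guess. Group-specific ESQ versions may also reveal the arm. All of this stands. A reader might infer that editing the letter would restore blinding, and the documents do not support that. It would still remove an explicit written statement, mainly for the attenders.
- **Bias is not demonstrated.** A reader might infer that the comparisons are biased, or that 80% of respondents are affected. The documents give no return rates and nothing from which size or direction could be derived. Knowledge items are also probably less open to expectation than satisfaction. Only a risk can be claimed.
- **The ratio has changed.** This moves the share from about 80% towards 76%, and the argument is unchanged.
- **Recruitment is well under way.** ESQs already sent cannot be repaired, and a mid-course change creates two regimes. This stands as a cost.

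**Conclusion.** The point holds as an avoidable risk to secondary, self-reported outcomes in a feasibility trial. About 80% of consenting participants at 2:1, or 76% at 4:1, would learn their group from the ESQ mailing before answering. These figures rest on the plan's 70% attendance forecast and on every navigation-arm non-attender being reached. With fewer reached, the share rises. The share among respondents is unknown, as are the size and direction of any response or non-response bias. Some 268 of the 307 are original-appointment attenders, in whom a spurious difference between arms is the most plausible consequence. The decision on whether navigation deserves a definitive trial does not depend on these comparisons.

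**What to change.** - Take the allocation sentence out of the ESQ cover letter. Disclose the group in a later letter, once the ESQ is back or the reminder window has closed.
- In every ESQ version, place the items common to both groups before any group-specific items, since these may reveal the arm.
- Record the date of the change. Earlier ESQs were sent with the disclosure, and the change may overlap with the move to 4:1, so the two periods should be distinguishable in the analysis.
- Report as limits that navigated participants know their group and that some usual-care non-attenders may guess it.
- Carry the later disclosure into the design of the definitive trial.

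The cost is a minor letter amendment, one additional letter, and two disclosure regimes within the same trial. Participants are still told their group, only later.
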